## Abstract

**Background:**

Acquired brain injury (ABI) can lead to biopsychosocial changes such as depression, low self-esteem and fatigue. These changes can cause, and be caused by, sexual issues affecting relationships and wellbeing. Given the relationship between sexual wellbeing and mental health, it is feasible that supporting sexual wellbeing will benefit psychological wellbeing. However, neurorehabilitation is inconsistent and often fragmented across the UK, and psychological, sexual and social support are lacking. Research shows that self-management and peer-support programmes can improve quality of life, self-efficacy and psychological wellbeing after brain injury. This protocol describes a feasibility randomised controlled trial (RCT) of a digital self-management programme to support mental and sexual wellbeing (known as HOPE4ABI), co-designed with and for people with ABI.

**Methods:**

This mixed-methods feasibility RCT has two parallel trial arms of the 8-week digital HOPE4ABI self-management programme. Eligibility criteria include age > 18 years, diagnosed or suspected ABI > 3 months prior to trial entry, access to an Internet-enabled device and ability to engage with the intervention. Referrals to the study website will be made via the National Health Service (NHS), social media and partnering organisations. Sixty eligible participants will be randomised at a ratio of 1:1 to peer-supported (*n* = 30) or self-directed (*n* = 30) HOPE4ABI programmes. Primary feasibility outcomes include recruitment and retention rates, engagement, adherence and usage. Secondary outcomes related to standardised measures of quality of life, sexual wellbeing and mental wellbeing. Participants and peer facilitators will be interviewed after the course to assess acceptability across both trial arms.

**Discussion:**

This feasibility trial data is not sufficiently powered for inferential statistical analyses but will provide evidence of the feasibility of a full RCT. Quantitative trial data will be analysed descriptively, and participant screening data representing age, ethnicity and gender will be presented as proportions at the group level. These data may indicate trends in reach to particular demographic groups that can inform future recruitment strategies to widen participation. Progression to a definitive trial will be justified if predetermined criteria are met, relating to recruitment, retention, engagement and acceptability.

**Trial registration:**

ISRCTN46988394 registered on March 1, 2023.

**Supplementary Information:**

The online version contains supplementary material available at 10.1186/s40814-023-01421-z.

## Background

Acquired brain injury (ABI) is an umbrella term referring to brain injury sustained after birth. Traumatic brain injury (TBI) and stroke account for the majority of UK ABIs (46% and 36%, respectively [1]), but other causes include brain tumour, encephalitis, meningitis and aneurysm. The UK prevalence of ABI is estimated at 2.5 million [2, 3] costing £41 billion per year [2, 4] in health and social care, lost work contributions and continuing disability [2]. ABI is a major cause of disability and disruption to families and society [5]. There are national campaigns in the UK to highlight the hidden impact and reduce the burden of ABI for patients and families [1, 6, 7], yet neurorehabilitation provision remains fragmented and inconsistent [1].

Sexual and reproductive health is integral to person-centred healthcare [8, 9] but is often neglected in neurorehabilitation [10–13]. This is commonly attributed to a lack of training opportunities and hence professional confidence and competence of healthcare practitioners [8], as well as patients’ reluctance to initiate discussions with healthcare professionals [12–14]. This results in limited opportunities for sexual (re)education and the formation and maintenance of intimate and social relationships after ABI [15].

Up to 75% of ABI survivors experience sexual problems [15, 16] totalling ~ 1.6 million people in the UK alone. Further, one in two report depression at 6 months [17], totalling ~ 1.2 million UK patients. There are complex interrelationships between neurological damage [18] and biopsychosocial changes (e.g. depression, anxiety, self-esteem [19]) following ABI. That is, biopsychosocial changes can cause—and be caused by—sexual issues [13, 20–22]. Depression has a profound impact on health and quality of life for people with ABI, resulting in more hospitalizations, less societal participation, reduced return-to-work rates, greater burden on caregivers and negative effects on social relationships [23]. Given the interrelationship between sexual health and mental health [13, 20–22], it is feasible that supporting sexual wellbeing will benefit psychological wellbeing.

Supported self-management is central to the NHS long-term plan [24] and involves professionals and patients jointly identifying needs, priorities and goals [25]. This process empowers patients with skills, knowledge and confidence to manage their own health and wellbeing. Post-stroke self-management interventions can lead to significant improvements in quality of life, self-efficacy, engagement in health-related behaviours, recovery from disability and participation in activities of daily living [26–30]. However, there are no self-management interventions for sexual wellbeing following brain injury. Likewise, peer-to-peer support approaches in neurorehabilitation have shown promising benefits, including increased behavioural control [31], self-efficacy and self-confidence; positive effects on quality of life by improving depressive symptoms, mood, psychological health and coping mechanisms; and increased knowledge, awareness and service engagement [12]. Educational resources for sex and relationships are available from many UK brain injury-related charities [10, 11, 32, 33], but lack interactive content and peer-to-peer exchange. There are currently no peer support programmes for sexual wellbeing after brain injury [12].

Patients generally attempt sexual activities 3–6 months post-ABI [16, 34], and post-3 months are, on average [35], patients’ preferred time to receive sexual information and support [36]. Digital technologies can support sexual education for patients and provide a solution to time constraints experienced by rehabilitation professionals [15]. For stigmatised topics such as sexuality, digital delivery allows autonomy, privacy and anonymity for the participant.

### Rationale

Owing to the novelty and sensitivity of the research area, it is not known whether a peer-supported intervention is an appropriate or acceptable forum for discussing sexual wellbeing after ABI. Owing to the personal nature of the topic, a self-directed intervention may be more suitable. With no comparative interventions to draw upon from research or practice, we propose a randomised controlled trial of a digital intervention, in two delivery formats: (i) peer-supported and (ii) self-directed. A feasibility RCT will address specific uncertainties, including willingness to be randomised, recruitment and retention rates, and acceptability of a sexual and mental wellbeing intervention [37–40], before conducting a definitive trial. As part of the acceptability assessment, we will also explore the appropriateness of mixed peer cohorts (e.g., whether participants would prefer peers to be of a similar age, ABI-type and/or gender).

## Methods/design

### Aim

The aim of this study is to assess the feasibility and acceptability of a digital peer-delivered intervention (HOPE4ABI) to support people with acquired brain injury to self-manage their mental and sexual wellbeing.

### Objectives

The primary objectives relate to assessing trial feasibility, via recruitment and refusal rates, retention and engagement rates for participation, and acceptability of trial procedures with a sample of participants and drop-outs for both arms of the trial. The secondary objectives will assess a preliminary signal of efficacy via pre-post change in scores on validated measures of mental wellbeing, quality of life and sexual wellbeing.

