### Trial design and setting

This is a mixed methods feasibility randomised control trial, with two parallel arms: (i) peer-supported HOPE4ABI (intervention group) and (ii) self-directed HOPE4ABI without peer support (control group). The study will be conducted online with UK-based participants, hosted on a secure bespoke online research management platform, eNgage; see [41]. Participant information, consent forms and questionnaires are administered online via Qualtrics Survey Software. Examples of the participant information sheet and consent form are provided in an additional file (see Additional file 1). The digital HOPE4ABI course will be hosted by Hope for The Community (H4C) Community Interest Company, a spinout social enterprise from Coventry University [42]. Analytics data on participant use of the HOPE4ABI courses is collected routinely by the H4C platform and will be used to inform engagement and usage patterns. All data from the research platforms and software (e.g., Qualtrics, H4C) is linked by the unique participant ID within eNgage.

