Week 6: Cognitive and mental wellbeing	• Understanding stress • Managing frustration • Low mood and worries • Recognising impulsivity • Brain fog—tips and tricks
Week 7: Emotional wellbeing	• Challenging unhelpful thinking styles • Building confidence and self-esteem • Mindful emotions • Self-compassion and caring for others • Reframing negative thoughts
Week 8: Living with hope	• Knowing your strengths • Happiness and hope • Building resilience • Planning meaningful activities

^a^*SMARTER* SMARTER is an acronym used by many organisations for goal setting and stands for Specific, Measurable, Achievable, Relevant, Time-bound, Enjoyable and Reward

The peer-supported HOPE4ABI course uses forums and messaging facilities that act as a conduit for communication between participants, peers and facilitators. The self-directed HOPE4ABI course contains all the same material but does not include peer support or interaction with other participants. In place of discussions, the self-directed course has a journal option for recording thoughts and making notes.

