### Secondary outcomes

Scores on validated questionnaires will indicate changes pre- and post-HOPE4ABI on mental wellbeing, quality of life and sexual wellbeing (summarised below). Whilst changes cannot be determined with any statistical significance in this study, we assess the feasibility of administering this set of questionnaires with a particular focus on acceptability and participant burden. Participants receive a £10 gift voucher for completing follow-up questionnaires at each of the timepoints T1 and T2. The schedule of enrolment, intervention and outcome measures is summarised in Table 3.

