#### Data analysis

All quantitative data from the study will be analysed descriptively in concordance with the CONSORT extension for pilot and feasibility trials [60]. Sociodemographic and screening data representing the age, ethnicity and gender of all participants screened, referred or refused will be presented as proportions at the group level. This data may indicate trends in demographic groups that the HOPE4ABI study does or does not appeal to and inform future recruitment strategies to widen participation.

Measures of mean and variance, including confidence intervals and standard deviations, and number and percent for categorical variables, will be used to describe the full range of secondary outcome data (i.e. participant wellbeing questionnaire scores) at baseline and T1 and T2 follow-ups. All quantitative analyses will be performed using SPSS Statistics.

Qualitative data will be analysed by a combination of deductive and inductive thematic analysis [61], as appropriate. Interview transcripts will be read multiple times by two researchers and coded independently by each researcher. An inter-rater reliability score (Cohen κ) of < 0.70 [62] will indicate all data should be coded by a third researcher. The researchers will generate, review and refine themes and any sub-themes emerging from the data, for each of the IG and CG groups. Data derived from novel or spontaneous contributions to the interview by the participant (e.g. matter relating to acceptability not directly asked by the researcher) will be inductively coded. Qualitative data analysis may be supported using NVivo software.

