## Discussion

HOPE4ABI is the first digital self-management intervention to support mental and sexual wellbeing after ABI. It is anticipated that this study will provide crucial evidence for the feasibility of conducting a national, multi-centre, 2 + arm, randomised controlled trial to confirm efficacy and effectiveness of HOPE4ABI for improving mental and sexual wellbeing. Through routinely collecting anonymous screening data at PIC sites, we can begin to understand any emerging trends in sample bias, for example, relating to age group, ethnic background or gender. This data will be used to inform recruitment strategies and accessibility issues in any future trials, to widen participation to diverse participant groups. Issues pertaining to equality, diversity and inclusion are more important than ever in healthcare, so addressing these from the outset is imperative to improving access to, and benefit from, services to all people. Progression to a definitive trial will be justified if predetermined criteria are met, relating to recruitment, retention, engagement and acceptability.

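### Pre-post change cannot serve as the efficacy signal when both arms receive HOPE4ABI; the stated estimate should be the randomised peer-support contrast

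*Protocol article*

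**What the plan says.** The Objectives section fixes both the aim and the measure: "The secondary objectives will assess a preliminary signal of efficacy via pre-post change in scores on validated measures". The Secondary outcomes section repeats the before-after framing: "Scores on validated questionnaires will indicate changes pre- and post-HOPE4ABI on mental wellbeing, quality of life and sexual wellbeing". It then adds that "changes cannot be determined with any statistical significance in this study".

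Trial design and setting names the peer-supported course as the intervention group and the self-directed course as the control group. Interventions describes what separates them: "The self-directed HOPE4ABI course contains all the same material but does not include peer support or interaction with other participants".

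For the questionnaire scores, Data analysis plans means, confidence intervals and standard deviations at baseline, T1 and T2. These "will be used to describe the full range of secondary outcome data". No between-arm difference is named for these outcomes in Objectives, Secondary outcomes or Data analysis. The only analysis stated separately for the two groups is that of the qualitative themes.

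**The concern.** A before-after change speaks to efficacy only if scores would otherwise have stayed where they were. This design has no group in which to see that, and the article itself gives reasons to expect movement:

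- Entry is allowed from 3 months after injury, with follow-up at 8 weeks and 6 months. The Background says patients generally attempt sexual activity again at 3 to 6 months, so early entrants are followed through a period of change.
- BIQS asks for current sexuality relative to pre-injury status, so ordinary recovery would move it.
- People may refer themselves to a wellbeing course when they feel low, which makes some regression to the mean plausible.
- The same questionnaires are repeated, and change is seen only in those who return them.

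If the objective is followed as written, a rise shared by both arms could be read as a sign that HOPE4ABI works. The Discussion looks ahead to a trial "to confirm efficacy and effectiveness of HOPE4ABI for improving mental and sexual wellbeing", and such a reading would feed the case for it. Meanwhile the comparison that randomisation protects, peer-supported against self-directed, is not named as a quantity to estimate.

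**Working it through.** **The plan's own figure.** There is none to reproduce. The sample of 60 (30 per arm) was set by reference to similar studies and guidelines, without an SD, effect size or error rate. The point does not depend on it.

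**Inputs from the article.** WEMWBS meaningful change 3 points (Mental wellbeing); 30 per arm planned (Sample size); 27 and 26 randomised (Trial status); retention criterion 75% (Transition to a definitive trial).

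**Assumptions, not in the article.** WEMWBS SD 8 to 10; baseline-follow-up correlation r 0.5 to 0.7 unless stated.

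**1. What pre-post change shows when the programme does nothing.** Give both arms the same drift and no effect, with SD 10, r 0.6 and 30 per arm.

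- SD of change = SD × √(2(1 − r)) = 10 × √0.8 = 8.94.
- Standard error of one arm's mean change = 8.94/√30 = 1.63.
- Standard error of the between-arm difference in change = 8.94 × √(2/30) = 2.31.

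Probability of reaching 3 points:

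| Common drift | One arm's pre-post change | Between-arm difference |
|---|---|---|
| 0 | z = 3/1.63 = 1.84, about 3% | z = 3/2.31 = 1.30, about 10% |
| 2 | z = 1/1.63 = 0.61, about 27% | about 10% |
| 3 | z = 0, 50% | about 10% |

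A simulation of 4,000 trials per setting agrees: 4%, 26% and 49% for one arm, and 11%, 10% and 9% between arms. Drift passes straight into the pre-post change and cancels in the randomised difference.

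**2. Regression to the mean.** Expected rise = (1 − r) × gap, where the gap is how far the entrants' mean baseline score lies below the mean of the population they come from, given selection through that score. For gaps of 3 to 8 points and r of 0.8 to 0.5, the rise runs from 0.2 × 3 = 0.6 to 0.5 × 8 = 4.0 points. The article gives neither the gap nor r and sets no entry threshold on a score, so the true size is unknown and could be small.

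**3. Precision of the randomised estimate.** Completers per arm at 75%: 0.75 × 27 = 20.25 and 0.75 × 26 = 19.5, so about 20.

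- Baseline-adjusted half-width = t(37) × SD × √(1 − r²) × √(2/20), with t(37) = 2.026.
  - SD 8, r 0.7: 2.026 × 5.71 × 0.316 = 3.66.
  - SD 10, r 0.5: 2.026 × 8.66 × 0.316 = 5.55.
- Unadjusted half-width = t(38) × SD × √(2/20), with t(38) = 2.024: 5.12 (SD 8) to 6.40 (SD 10).
- With 30 per arm and no loss, the adjusted half-width (using 1.96) would be 2.89 to 4.38.

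Adjustment helps, but at 20 completers per arm the interval still extends more than 3 points either side of the estimate.

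**The case against.** The strongest reply is that this is a wording matter in a feasibility study. The article says the data are not powered for inference, makes all quantitative analysis descriptive, and directs the secondary outcomes mainly at whether the questionnaires can be administered acceptably. The progression criteria are recruitment, retention, engagement and acceptability. All of this stands, and it limits the consequence. It does not dispose of the point: low power and lack of significance concern random error, while drift shared by both arms is a bias that a larger sample would leave in place.

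Several stronger readings are tempting and are not supported:

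- *That the randomised contrast will go unused.* The article names no such contrast, but it has a blinded analyst for the quantitative outcomes and follows the CONSORT extension for pilot trials. By-arm reporting is not excluded, and the full protocol and any SAP are not shown.
- *That Secondary outcomes contradicts Objectives.* It rules out statistical significance. A tentative signal without significance is compatible with that.
- *That planning SDs would not be produced.* Data analysis provides for them. Only the adjusted difference and the baseline-follow-up correlation are unnamed.
- *That the trial must explore a no-programme arm.* The Discussion leaves the arms of the future trial open, so this concerns a design not yet specified.
- *That regression to the mean would by itself reach 3 points.* This needs assumptions at the unfavourable end, and the article supports none of them.
- *That the trial says nothing about HOPE4ABI.* The Aim describes the intervention as peer-delivered, and the randomised contrast does inform on that component.

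It is also fair to say that a between-arm estimate will be imprecise, and that missing follow-up could bias it. It is the randomised comparison, not a guaranteed unbiased one.

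**Conclusion.** The point holds in a limited form. The objective ties the efficacy signal to pre-post change in a trial where every participant receives the programme material, and that change cannot be attributed to HOPE4ABI. The conclusion follows from the design and needs none of the numerical assumptions. They serve only to show scale: under no effect and an assumed 3-point drift, one arm's change reaches the meaningful threshold in about 50% of trials, against about 10% for the between-arm difference. The real drift, including any regression to the mean, is unknown.

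The importance is moderate. The stated objective should be corrected because it names the wrong quantity, but the error affects a secondary objective and no decision to progress depends on it.

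**What to change.** 1. In Objectives, and in the matching sentence of Secondary outcomes, stop describing pre-post change as a signal of efficacy. Present within-arm change as description only.
2. Restate the secondary objective as: to estimate, with 95% CI and no hypothesis test, the baseline-adjusted difference (peer-supported minus self-directed) in WEMWBS, QOLIBRI-OS and BIQS at T1 and T2, together with the baseline-follow-up correlation for planning.
3. In Data analysis, name the method: one ANCOVA per outcome and time point with the baseline score as covariate, in all randomised participants with data.
4. State that the estimate informs only the added effect of peer support, not the effect of HOPE4ABI against no programme.

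**Cost.** Three outcomes at two times give six estimates from data already being collected; no new measure is needed. The efficacy claim becomes weaker, and the intervals will be wide against the 3-point threshold and should be reported as such. Randomisation had taken place and the intervention phase was underway at re-submission, so the change should be dated and recorded as made before the outcome data are analysed. If an existing SAP already specifies this contrast, only the wording of the objective needs to be brought into line with it.

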### Trial design and setting

This is a mixed methods feasibility randomised control trial, with two parallel arms: (i) peer-supported HOPE4ABI (intervention group) and (ii) self-directed HOPE4ABI without peer support (control group). The study will be conducted online with UK-based participants, hosted on a secure bespoke online research management platform, eNgage; see [41]. Participant information, consent forms and questionnaires are administered online via Qualtrics Survey Software. Examples of the participant information sheet and consent form are provided in an additional file (see Additional file 1). The digital HOPE4ABI course will be hosted by Hope for The Community (H4C) Community Interest Company, a spinout social enterprise from Coventry University [42]. Analytics data on participant use of the HOPE4ABI courses is collected routinely by the H4C platform and will be used to inform engagement and usage patterns. All data from the research platforms and software (e.g., Qualtrics, H4C) is linked by the unique participant ID within eNgage.

